In light of these evidences, we designed a pilot randomized controlled clinical trial to investigate the feasibility, safety, and efficacy of high-dose iTBS in children with ASD. We hypothesize that high-dose iTBS may be a feasible and safe rTMS protocol for children with ASD. A 4-week high-dose iTBS intervention, compared to sham stimulation, is expected to result in significant improvements in core autistic symptoms, alterations in resting-state functional connectivity, and changes in salivary levels of oxytocin, growth hormone, IGF-1, and IGFBP-3.

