
### Assignment of interventions

This is a double-blind randomized clinical trial. The randomization of participants will be conducted using a computer-generated random list, based on the permutation block method with a random number generator. The ratio of participants allocated to each group will be 1:1. The allocation sequence was concealed by a research assistant using sealed, opaque envelopes that contained the treatment information prior to the study’s official commencement. Once the consent form and baseline measures have been completed, an envelope for a participant ID number will be provided to the rTMS therapist prior to the first iTBS session. The rTMS therapist is the sole individual responsible for determining the treatment method (iTBS or sham-iTBS), and he/she does not perform assessments or statistical analyses. It is imperative that other study researchers, participants, parents/guardians, and statistical analysts, remain completely blinded to the treatment condition. Any adverse or discomfort event will be recorded after each iTBS treatment session. If a participant experiences a serious adverse event, the blindness will be removed.

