### Sample size and recruitment

Forty children diagnosed with ASD will be included in total (iTBS group, n = 20; sham group, n = 20). Whilst a formal sample size calculation is not required in a pilot study (54), it is recommended that a sample size of between 15 and 20 participants is maintained for the purpose of conducting a subsequent full-scale study (55). In consideration of a potential dropout rate of 15%, the objective was to recruit a total of 48 participants. Nonetheless, we will endeavor to recruit a greater number of participants if feasible within the time and resources available. All participants will be recruited from the China Autism Rehabilitation Research Center, Beijing Boai Hospital, where advertisements will be posted to attract potential participants. One researcher will conduct the recruitment process, during which he/she will document the participants’ medical histories, including past and current medical conditions.

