### Outcome measures

For the first study objective, to determine feasibility and safety, we will report the recruitment rate, adherence rate, completion rate, and adverse reactions. The recruitment rate will be reported as the percentage of eligible ASD children who will participate in the study and the number of subjects recruited monthly over the recruitment period. The adherence rate will be measured by the proportion of participants who complete the intervention as planned. The completion rate will be assessed by the proportion of participants who complete all assessments and follow-ups. Safety will be assessed by comparing the rates of drop-outs attributed to adverse events and the rates of serious adverse events. For the second study objective, to determine the potential efficacy of the iTBS intervention on ASD, our endpoints include the Autism Behavior Checklist (ABC), Social Responsiveness Scale, 2nd Edition (SRS-2), Childhood Autism Rating Scale (CARS), Autism Treatment Evaluation Checklist (ATEC) and the Repetitive Behavior Scale-Revised (RBS-R). The ABC scale consists of 57 items that involve a range of typical autistic behaviors. These items are categorized into five domains including relating, sensory, language, body use and object manipulation, and social and self-help. Each item contained its own score ranging from 1 to 4 points according to the item weights, and higher total scores indicate more severe ASD symptoms (56) The SRS-2 is a norm-referenced quantitative assessment comprising 65 items pertaining to children’s behavioral characteristics. Parents or caregivers are required to rate five subdomains, namely social awareness, social cognition, social communication, social motivation, and restricted repetitive behaviors (57). The CARS was developed as an observational rating scale to capture ASD symptoms through parent/carer interviews, observations, and case reviews. Each item is scored from 1 to 4, with 1 representing appropriate behavior and 4 representing behavior that deviates severely from normal criteria, so higher total scores indicate more severe ASD symptoms. This tool can be utilized to display the overall symptom severity of ASD (58). The participant’s parent needs to complete the ATEC questionnaire, which is comprised of four subscales (speech/language communication, sociability, sensory/cognitive awareness, and physical/health/behavior). The ATEC has been used to measure treatment effects, with a lower score indicating a lower severity of ASD symptoms (59). The RBS-R was a valid tool for assessing repetitive and stereotypic behaviors in children with ASD, including six parts: stereotyped behaviors (6 items), self-injurious behaviors (8 items), obsessive-compulsive behaviors (8 items), ritualistic behaviors (6 items), fixation behaviors (11 items), and restrictive behaviors (4 items). The scale uses a 0-3 scoring system: 0 for no behavioral problems, 3 for severe, 2 for moderate, and 1 for mild (60).

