### Data analysis plan

All statistical analyses will be performed using IBM SPSS 26.0 by independent blinded statisticians. Chi-squared tests and t-tests will be performed for the categorical and continuous variables, respectively, to examine the group differences in the demographics and clinical profiles between the two groups at baseline. To assess for significant differences in treatment effects over time, a mixed-effects model with predictor variables for group (rTMS condition: active vs placebo) and time (baseline vs. end of treatment vs. follow-up) will be fitted to the data from the outcome measures. The effect size between groups will also be calculated. The feasibility and safety outcomes will be presented as proportions, and we will compare the rates between the two groups. All significance levels will be set at P < 0.05.

The EEG signals are preprocessed using the EEGLAB toolbox under MATLAB R2022b. A finite impulse response filter is constructed with a lower edge frequency of 1 Hz and a higher boundary frequency of 45 Hz. In order to artifacts induced by excessive body movements, we will perform an initial visual inspection of the EEG data. An independent component analysis will be conducted to remove additional artifacts. The segmentation will divide the EEG signals into epochs of 2s. The absolute and total power of the four frequency bands (δ, θ, α, and β) are calculated separately using the fast Fourier transforms. Then, the relative power of channels in these frequency bands will be calculated using MATLAB R2022b to analyze the changes in brain functional network characteristics before and after the intervention, including the magnitude squared coherence, phase locking value, phase lag index, and weighted phase lag index.

The NirSpark software package (Danyang HuiChuang Medical Equipment Co., Ltd., Zhenjiang, China) was used to analyze the fNIRS data. Following the conversion of the raw data to optical density signals, the motion artifacts will be reduced through the utilization of cubic spline interpolation. The obtained signals are filtered with a band-pass (0.01 to 0.2 Hz) filter in accordance with Butter’s law, to eliminate physiological noise generated by heartbeat and respiration. After preprocessing, the optical density will be converted to concentrations of oxyhemoglobin, deoxyhemoglobin, and total hemoglobin based on the Beer-Lambert law.

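### A P < 0.05 comparison of rare harm rates with 20 to 24 children per arm cannot support a conclusion that high-dose iTBS is safe; exact intervals should carry the safety conclusion

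*Protocol article*

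**What the plan says.** The Introduction gives the hypothesis: "We hypothesize that high-dose iTBS may be a feasible and safe rTMS protocol for children with ASD". Outcome measures places safety with feasibility in the first study objective and says how it is judged: "Safety will be assessed by comparing the rates of drop-outs attributed to adverse events and the rates of serious adverse events". The Data analysis plan adds "The feasibility and safety outcomes will be presented as proportions, and we will compare the rates between the two groups", followed immediately by "All significance levels will be set at P < 0.05".

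On size, Sample size and recruitment says "Forty children diagnosed with ASD will be included in total (iTBS group, n = 20; sham group, n = 20", on the ground that "a formal sample size calculation is not required in a pilot study". It continues: "In consideration of a potential dropout rate of 15%, the objective was to recruit a total of 48 participants". Assignment of interventions fixes equal allocation.

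Other parts of the article also bear on this:
- Adverse reactions are to be reported (Outcome measures).
- Any adverse or discomfort event is recorded after each session (Assignment of interventions).
- Adverse events are monitored from consent to the last visit (Safety monitoring).
- The chi-squared test is named only for baseline characteristics. No test is named for the safety comparison.
- The Discussion gives a general caution that the sample may be too small to detect group differences. It does not mention safety.

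**The concern.** A significance test of two rates looks for a difference. Failing to find one is informative only if the test would probably have found a difference that matters. The two safety endpoints are expected to be rare: the Introduction cites earlier adverse events as mild and transient. With about 20 children per arm, the comparison is non-significant over most of the range of harm that anyone would want to know about. A non-significant result therefore says little about whether the protocol is safe.

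The participants are children aged 2 to 10 who are due to receive 108,000 pulses in total. The Introduction itself says that paediatric safety data at high dose are relatively lacking, and the results are meant to inform larger trials. What those trials need from this one is a statement of how much harm has been excluded. A P value does not give that.

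**Working it through.** **Inputs.** 20 per arm, 1:1 allocation, 15% dropout and 48 recruited (Sample size and recruitment; Assignment of interventions); significance at P < 0.05 (Data analysis plan). Assumptions: two-sided tests, since sidedness is not stated, and 0, 1 or 2 sham events, since the article gives no expected rate for either endpoint.

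**1. The article's own figure.** 40 / (1 − 0.15) = 47.06, rounded up to 48, or 24 per arm. This reproduces. Both 20 and 24 per arm are used below. Children who drop out because of adverse events belong in the denominator, so 24 is the natural base for that endpoint if all 48 are randomised.

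**2. Smallest significant count with no sham events.** For k of n active against 0 of n sham:
- Uncorrected chi-squared = 2nk / (2n − k), to be compared with 3.84.
- Two-sided Fisher P = 2 × C(n, k) / C(2n, k).

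| Active vs sham | Chi-squared P | Fisher P |
|---|---|---|
| 3/20 vs 0/20 | 120/37 = 3.24, P = 0.072 | 2 × 1140/9880 = 0.231 |
| 4/20 vs 0/20 | 160/36 = 4.44, P = 0.035 | 2 × 4845/91390 = 0.106 |
| 5/20 vs 0/20 | 200/35 = 5.71, P = 0.017 | 2 × 15504/658008 = 0.047 |

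The threshold is 4/20 (20%) by chi-squared and 5/20 (25%) by Fisher. A continuity-corrected chi-squared needs 6/20 (30%, P = 0.027). At 4 against 0 the choice of test changes the result.

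With 24 per arm the thresholds are 4/24 (17%; 192/44 = 4.36, P = 0.037) and 5/24 (21%; Fisher P = 0.0496).

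**3. Sham events raise the threshold.** With 20 per arm, one sham event moves it to 6/20 (chi-squared, P = 0.037) or 7/20 (Fisher, P = 0.044), that is 30 to 35%. Two sham events move it to 8/20 or 9/20, that is 40 to 45%.

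**4. Power, 20 per arm, true sham rate 0.** This is the binomial probability of at least 5 (Fisher) or at least 4 (chi-squared) events in 20.

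| True active rate | Fisher | Chi-squared |
|---|---|---|
| 5% | 0.3% | 1.6% |
| 10% | 4% | 13% |
| 20% | 37% | 59% |
| 25% | 59% | 78% |

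**5. What an interval would show.** For zero events the exact (Clopper-Pearson) two-sided 95% upper limit is 1 − 0.025^(1/n).
- n = 20: 16.8%.
- n = 24: 14.2%.

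For 3/20 the exact 95% interval is 3.2% to 37.9%, while the comparison with 0/20 is non-significant by either test.

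**The case against.** The strongest case against the point is that a reader might infer more than the article says. Four stronger readings are tempting, and none is supported.

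- **That a non-significant result will be declared safe.** No sentence says so. The hypothesis is worded tentatively, and the Discussion presents the trial as a source of pilot data.
- **That the comparison is the only safety assessment.** It is not. Proportions will be presented, adverse reactions reported and events recorded after each session. Three of 20 against none would appear as 15% against 0%.
- **That an invalid chi-squared test is planned for sparse safety data.** Chi-squared is assigned only to baseline variables. The safety test is unnamed, and naming it could be left to a statistical analysis plan.
- **That the absence of planned intervals is itself a fault.** This is a journal article, and such detail may stand in a fuller document.

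It is also fair to say that a pilot needs no power calculation, that the small size is disclosed, and that 20 per arm may not be the right denominator.

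All of this stands as a limit on the point, but it does not remove it. Outcome measures defines the safety assessment as the comparison, and the blanket significance level covers that comparison. This is a stated criterion, not an omitted detail, and it does not suit the hypothesis whichever test is chosen. The Discussion's caveat is general and does not say how a null safety comparison should be read. Using 24 per arm changes the figures and leaves the conclusion as it is.

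**Conclusion.** The point holds in a limited form. The stated safety criterion, a between-arm comparison at P < 0.05, cannot support the hypothesis that the protocol is safe. In the most favourable case, with no sham events, it reaches significance only when 20 to 25% of active children have an event (20 per arm) or 17 to 21% (24 per arm). Any sham event raises the threshold.

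These figures assume two-sided testing by uncorrected chi-squared or Fisher's exact test, and sham counts that the article does not give. The sample size is not criticised; it is acceptable for a pilot. The fault lies in the inferential criterion. Severity: should fix. Design, conduct and data collection are unaffected.

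**What to change.** Reword Outcome measures and the Data analysis plan so that the safety comparison is descriptive:

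- For each arm, with all randomised (or all treated) children as the stated denominator, report the number and proportion with a serious adverse event and with an adverse-event drop-out, each with an exact (Clopper-Pearson) 95% confidence interval.
- Report the risk difference with a score-type (Newcombe) or exact 95% confidence interval.
- State that P > 0.05 supports no safety conclusion, and that the conclusion will quote the upper limit of the active-arm rate (for zero events, 16.8% with 20 children or 14.2% with 24).
- If a P value is shown, use Fisher's exact test.

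The cost is about one paragraph of wording, with no new data. The downside is a less favourable safety statement, because it will say openly how much harm has not been excluded.

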**Methods:**

A randomized controlled pilot trial with a 4-week intervention will be conducted. Forty children with ASD will be randomized into either the intervention or control group. The intervention group will receive 5400-pulse iTBS per day, while the control group will receive sham iTBS. Feasibility will be evaluated through recruitment, intervention adherence, and assessment completion. Safety will be assessed by comparing the rates of drop-outs attributed to adverse events and the rates of serious adverse events The efficacy outcomes include the Autism Behavior Checklist, Social Responsiveness Scale, 2nd Edition, Childhood Autism Rating Scale, Autism Treatment Evaluation Checklist and Repetitive Behavior Scale-Revised. Resting-state electroencephalogram and functional near-infrared spectroscopy will be employed to quantify alterations in functional brain connectivity and cerebral haemodynamics. Salivary levels of oxytocin, growth hormone, insulin-like growth factor 1, and insulin-like growth factor binding protein 3 are measured to reflect the biochemical response to iTBS. These indicators will be assessed at baseline and at the end of the intervention.

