
Salivary levels of oxytocin, growth hormone, IGF-1, and IGFBP-3 are measured by ELISA to reflect the biochemical response to treatments. A number of studies have demonstrated that the ELISA is capable of testing the concentration of oxytocin, growth hormone, IGF-1, and IGFBP-3 in human saliva (61–63). The ELISA kits are purchased from Shanghai Enzyme-linked Biotechnology Co., Ltd. (Shanghai, China). The parents/legal guardians were requested to ensure that their children refrained from eating, drinking, and oral cleaning for at least an hour before saliva collection. Subjects were instructed to spit at least 0.5ml of saliva into a disposable saliva collector. If a child is unable to carry out this instruction, the researchers will use a disposable pipette to extract his/her saliva. To eliminate any potential bias due to circadian rhythms, all salivary samples were collected between 4 and 5 p.m. Each sample was centrifuged and the resulting supernatant was divided into Eppendorf tubes and frozen at -80°C. At the end of the trial, the saliva samples will be irrevocably destroyed.

Resting-state EEGs will be recorded for 10 minutes using the CURRY 8.0 software in a 64-channel Neuroscan system (Compumedics Neuroscan, Victoria, Australia). An EEG cap with saline electrodes is used (GREENTEK, Wuhan, China) based on the international 10-20 system, which is easy to apply and does not necessitate gel applications. The data are acquired at a sampling rate of 1 kHz, and the impedances are maintained at a level below 50 kΩ. All the children need to be awake and relaxed during the EEG recordings. Three types of caps (extra small, small, and medium) will be prepared for them.

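### No efficacy outcome leads and one P < 0.05 threshold covers all tests: under no effect, the chance of at least one false positive is about 23% over the five scales and up to 37% with saliva

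*Protocol article*

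**What the plan says.** The Outcome measures section of the protocol article puts feasibility and safety first and potential efficacy second. For efficacy, the abstract reads: "The efficacy outcomes include the Autism Behavior Checklist, Social Responsiveness Scale, 2nd Edition, Childhood Autism Rating Scale, Autism Treatment Evaluation Checklist and Repetitive Behavior Scale-Revised". Outcome measures gives the same five scales as endpoints, and neither place says which one leads.

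Outcome measures then adds biological measures: "Salivary levels of oxytocin, growth hormone, IGF-1, and IGFBP-3 are measured by ELISA", a 64-channel resting EEG, and a 54-channel resting fNIRS recording. The Data analysis plan describes EEG power in four frequency bands and network characteristics "including the magnitude squared coherence, phase locking value, phase lag index, and weighted phase lag index".

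In the same section, a mixed-effects model with group and time "will be fitted to the data from the outcome measures". The time factor is given as "time (baseline vs. end of treatment vs. follow-up", whereas the abstract says "These indicators will be assessed at baseline and at the end of the intervention". Between-group effect sizes are also planned. The paragraph closes with: "All significance levels will be set at P < 0.05".

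The Introduction states the hypothesis: four weeks of high-dose iTBS, compared with sham, "is expected to result in significant improvements in core autistic symptoms, alterations in resting-state functional connectivity, and changes in salivary levels" of the four analytes.

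**The concern.** The per-test threshold limits the error of each comparison to 5%. It does not limit the error of the efficacy claim as a whole, because the article does not say which comparison carries that claim. With five scales of equal standing, a result below 0.05 on any one could be presented as the predicted significant improvement. The choice could be made after the results are known.

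This matters even in a pilot. The article says its data are meant to inform the design of a larger trial. A scale picked because it happened to cross 0.05 with 20 children per arm is a poor basis for that trial's primary outcome, and its effect size will tend to be exaggerated.

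**Working it through.** **Figures in the article.** It gives no family-wise error rate and no power, so there is no such figure to reproduce. Its one calculated figure, the recruitment target, does reproduce: 20/(1 − 0.15) = 23.5, rounded up to 24 per arm, or 48 in total. That figure does not bear on error control.

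**Inputs.** Per-test level 0.05 (Data analysis plan; sidedness not stated, two-sided assumed). Five scales and four analytes (Outcome measures). One post-baseline contrast per outcome if the abstract is followed, two if the model's three time levels are. Baseline, feasibility and safety comparisons are not counted.

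**Independent tests.** The chance of at least one P < 0.05 under no effect is 1 − 0.95^k.

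- Five scales: 1 − 0.95^5 = 1 − 0.774 = 22.6%.
- Four analytes: 1 − 0.95^4 = 1 − 0.815 = 18.5%.
- All nine: 1 − 0.95^9 = 1 − 0.630 = 37.0%.

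**Correlated tests.** Scales that rate the same children will be correlated, and the article gives no correlations. I simulated two-sided z-tests with an assumed common correlation r (100,000 replicates per cell):

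| Tests | r = 0 | r = 0.3 | r = 0.5 | r = 0.7 |
|---|---|---|---|---|
| 5 scales | 23% | 21% | 18% | 15% |
| 9 (scales + saliva) | 37% | 33% | 27% | 20% |
| 18 (the nine at two times) | 60% | 51% | 40% | 28% |

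Suppose instead that scales correlate only with scales and analytes only with analytes. The nine-test figure is then 33% (scales 0.5, analytes 0.3), 30% (0.7, 0.3) or 28% (0.7, 0.5).

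**Time points.** The 18-test row applies only if a follow-up visit exists and both post-baseline contrasts are tested. The abstract and the Data analysis plan differ on this, so the number of contrasts is itself unclear.

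**EEG and fNIRS, illustration only.** Assume one whole-head summary per measure: 4 bands × 4 indices = 16, plus 4 band powers, plus 3 haemoglobin signals. Added to the nine, that makes 9 + 16 + 4 + 3 = 32 tests. The chance is then 1 − 0.95^32 = 80.6% if independent, and 68%, 52% and 35% at r = 0.3, 0.5 and 0.7. The article does not state this count.

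**How many tests make a false positive nearly certain.** With independent tests, 90% needs ln(0.10)/ln(0.95) = 44.9, so 45 tests. For 95% it is ln(0.05)/ln(0.95) = 58.4, so 59 tests.

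**The case against.** The strongest reply is that this is a pilot and says so. Efficacy is the second objective and is called potential and preliminary. No formal sample size calculation is claimed, and the Discussion admits that the sample may be too small to show group differences and that larger studies will be needed. Effect sizes are already planned. The hypothesis joins symptoms, connectivity and saliva with *and*, so it does not say that any single result below 0.05 would confirm it. Region selection and correction within EEG or fNIRS families commonly sit in an analysis plan, which is not shown.

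Most of this stands and limits the point. It does not remove it. The article does not leave the threshold open: it fixes one level for all tests, and a later plan with error control would have to qualify that sentence. Which efficacy scale leads is a protocol-level choice, and the section that lists the endpoints does not make it. The wording of the hypothesis also goes beyond a preliminary look.

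A reader might infer three stronger claims, none of which the article supports:

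- *A false positive is almost guaranteed.* That needs about 45 to 59 roughly independent tests. The nine outcomes listed as single measures give 37% at most with one contrast each.
- *EEG and fNIRS will be tested channel by channel.* One can multiply out 64 × 63/2 = 2,016 channel pairs × 4 bands × 4 indices = 32,256 EEG tests, and 54 × 3 = 162 fNIRS tests. The article describes no such testing. Its fNIRS text stops at conversion to haemoglobin concentrations, and the Figure 3 caption refers to an area of interest.
- *The trial has no lead outcome at all.* Feasibility and safety lead. What is missing is a lead efficacy outcome.

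**Conclusion.** The point holds as a gap in the efficacy objective. No scale or time point leads, a single 0.05 threshold applies throughout, and the introduction predicts significance. Under no effect, the chance of at least one nominally significant result is about 23% over the five scales and up to 37% over scales plus saliva, against a nominal 5%. These are upper values that assume independence, two-sided tests and one post-baseline contrast per outcome. At assumed correlations of 0.3 to 0.7 the nine-outcome figure is about 33% to 20%. Uncorrected EEG and fNIRS tests would raise the risk by an amount that the article does not allow one to fix. Because this is an openly preliminary pilot, the change is one that should be made; the gap does not undermine the trial's first objective.

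**What to change.** Before unblinding:

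1. Name one lead efficacy scale and one time point, both the sponsor's choice, and test that comparison at 0.05. The error for the lead claim is then 5%.
2. Report the other scales and the four analytes as between-group differences with 95% confidence intervals, labelled exploratory and without significance claims.
3. Label EEG and fNIRS exploratory. If p-values are shown, control them within each family by a stated method; which method is open.
4. Replace the sentence that sets every significance level at 0.05 with wording to match.

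A correction across the scales would also control the error, at 0.05/5 = 0.010 for the scales or 0.05/9 = 0.0056 with saliva, but it costs more. With 20 per arm and an assumed standardised difference of 0.8, power by normal approximation falls from 72% at 0.05 to 48% at 0.010 and 40% at 0.0056. One lead outcome keeps the 72% for the comparison that matters most.

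The cost is protocol wording, with no extra visits, participants or measurements. The downside is that fewer results can be called significant.

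### Uncorrected EEG connectivity indices could pick up differences in the amount of clean data, mainly in the before/after reading, if they are estimated across epochs

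*Protocol article*

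**What the plan says.** The Outcome measures section plans that "Resting-state EEGs will be recorded for 10 minutes using the CURRY 8.0 software in a 64-channel Neuroscan system" and asks that the children be awake and relaxed. The Data analysis plan then gives the processing order. After a 1 to 45 Hz filter, and with movement artefact as the stated reason, "we will perform an initial visual inspection of the EEG data". Next, "An independent component analysis will be conducted to remove additional artifacts". Then "The segmentation will divide the EEG signals into epochs of 2s". After FFT power in four bands, the stated aim is "to analyze the changes in brain functional network characteristics before and after the intervention". The indices meant by this are then listed as "including the magnitude squared coherence, phase locking value, phase lag index, and weighted phase lag index".

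For outcome measures in general the same section plans "a mixed-effects model with predictor variables for group (rTMS condition: active vs placebo) and time".

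The section names the four indices in their raw form. It does not say whether each is estimated across epochs or within epochs and then averaged. It gives no number of epochs per recording, and it does not say in words that contaminated data are cut out.

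**The concern.** All four indices are non-negative. When estimated across a finite number of epochs, each has a positive expected value even if two channels are unrelated, and that floor rises as the number of epochs falls. Two recordings with the same brain coupling but different amounts of usable data then give different values, and the recording with less clean data shows the higher apparent connectivity.

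The participants are children with ASD aged 2 to 10 years, and the protocol itself expects restlessness: it provides for comforting, acclimation to the room and rest breaks. The yield of clean data can be expected to vary between children, and it may rise between visits as children get used to the setting. If so, the indices would fall after treatment with no change in coupling.

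Altered resting-state functional connectivity versus sham is a stated hypothesis in the Introduction, and the results are meant to inform larger trials. A fall caused by better cooperation could be read as modulation of brain networks.

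**Working it through.** **Inputs.** Recording length is 10 minutes (Outcome measures) and epoch length 2 s (Data analysis plan). The largest possible number of non-overlapping epochs is 600 s / 2 s = 300. The documents give no retained count, no connectivity value and no bias figure, so there is no figure of the plan's own to reproduce. The counts below are assumptions within the range 20 to 300.

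**Floor under across-epoch estimation, no true coupling.** For n independent epochs the expected values are approximately:

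- coherence: 1/n
- PLV: √(π/(4n))
- PLI: √(2/(πn))

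For n = 60 these give 0.0167, 0.114 and 0.103. For n = 200 they give 0.005, 0.063 and 0.056. A simulation with complex Gaussian Fourier coefficients (13,333 to 20,000 replicates per setting) agrees and adds wPLI:

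| Epochs | Coherence | PLV | PLI | wPLI |
|---|---|---|---|---|
| 30 | 0.033 | 0.162 | 0.144 | 0.204 |
| 60 | 0.017 | 0.115 | 0.103 | 0.146 |
| 100 | 0.010 | 0.089 | 0.080 | 0.113 |
| 200 | 0.005 | 0.062 | 0.056 | 0.079 |
| 300 | 0.003 | 0.051 | 0.046 | 0.065 |

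A child with 60 clean epochs at baseline and 200 after treatment would show falls of 0.017 − 0.005 = 0.012, 0.115 − 0.062 = 0.053, 0.103 − 0.056 = 0.047 and 0.146 − 0.079 = 0.067.

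**With real coupling at a phase lag of π/4, same change from 60 to 200 epochs.**

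| True coherency | Coherence | PLV | PLI | wPLI |
|---|---|---|---|---|
| 0.3 | 0.104 to 0.094 | 0.256 to 0.243 | 0.222 to 0.217 | 0.411 to 0.413 |
| 0.5 | 0.259 to 0.252 | 0.416 to 0.409 | 0.378 to 0.378 | 0.655 to 0.659 |

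The largest fall is 0.013, and wPLI hardly moves.

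**With real coupling at zero lag.** PLI and wPLI ignore zero-lag coupling by design, so these pairs stay at the floor however strong the coupling. With coherency 0.5 at zero lag, going from 50 to 200 epochs moves PLI from 0.113 to 0.057 and wPLI from 0.160 to 0.080.

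**Within-epoch estimation.** If PLV and PLI are computed inside each 2-s epoch and averaged (8 to 13 Hz, no coupling), the means at 30, 60, 150 and 300 epochs are 0.253, 0.251, 0.250 and 0.251 for PLV, and 0.212, 0.210, 0.211 and 0.210 for PLI. The floor is higher but does not depend on the count. Coherence cannot be computed this way from one FFT per epoch, because coherence from a single segment is identically 1. It must be averaged over segments, and the only segments the plan names are the 2-s epochs.

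**Before/after versus active-versus-sham.** Take PLV with no coupling. If both arms go from 60 to 200 epochs, each arm falls by 0.053 and the difference between arms is 0. If the active arm goes from 60 to 200 and the sham arm from 60 to 100, the changes are −0.053 and 0.089 − 0.115 = −0.026, a spurious contrast of −0.027. If sham stays at 60, the contrast is −0.053.

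**The case against.** The strongest case against is that this is an omission from a condensed article. Epoch counts and estimator variants are signal-processing detail that a full protocol or analysis plan may hold, and 2-s epochs are compatible with an equal number of them per recording. This stands in part. The article is silent on the count and on the estimator, so no error is demonstrated. It does, however, commit to four named indices in raw form, and a better-behaved form of them can be specified at once.

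It can also be objected that no epoch rejection is described, since inspection and ICA come before segmentation and ICA removes components, not epochs. Removal of data is indeed only implied: the inspection is aimed at movement artefact, and ICA is there for what remains. The order matters little, because cutting continuous data before segmentation also leaves fewer epochs.

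Third, randomisation and a sham coil that imitates the sensations of treatment mean that acclimation common to both arms cancels on average in the group contrast. This stands. It does not protect the before/after reading. Nor would it protect the contrast if active treatment itself made children stiller, which is possible if core symptoms improve as hypothesised.

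Finally, the size depends on weak or zero-lag coupling and on assumed counts, and it has not been set against between-child variability. That also stands.

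A reader might go further and infer that differences in how still the children sit will be reported as connectivity changes, or that the planned EEG comparison of active with sham is invalid. The documents do not support this. They do not state that the indices come from whatever epochs survive rejection, do not fix across-epoch estimation, and give no evidence that stillness will change differently by arm.

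**Conclusion.** The concern holds in a conditional form. It needs two things: across-epoch estimation, which is the natural reading for FFT-based coherence but open for PLV, PLI and wPLI; and clean-data yields that differ by visit or arm. Under both, the bias could appear as a connectivity change, mainly in the before/after reading and in pairs that are weakly coupled or, for PLI and wPLI, coupled at zero lag. For those pairs, a three- to fourfold change in epochs shifts PLV, PLI or wPLI by about 0.05 to 0.08 and coherence by 0.012 to 0.015. With phase-lagged coherency of 0.3 or more, the shift is 0.013 or less. The actual size in this trial is unknown.

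EEG is a mechanistic measure in a pilot whose first objective is feasibility and safety, so nothing essential to the trial is at risk. The change is still worth making, because connectivity is one of the stated hypotheses and the remedy is cheap.

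**What to change.** State in the EEG analysis how each index is estimated, and adopt one of three routes before unblinding:

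1. Use forms whose expectation does not depend on the number of epochs: debiased wPLI, pairwise phase consistency in place of PLV, and bias-corrected coherence. In the simulation, debiased squared wPLI had a null mean between −0.002 and 0.000 for every n from 20 to 300. PLI can be treated like PLV, by correcting its square as (n·PLI² − 1)/(n − 1).
2. Compute the indices within epochs of fixed length and average them. Coherence then needs sub-windows or tapers inside each epoch.
3. Draw at random a common, low number of clean epochs from every recording. With equal counts and the same underlying coupling, the artificial difference is 0.

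Whichever route is taken, report the number of clean epochs by arm and visit. Keep short recordings in the analysis through the debiased forms. Excluding them after randomisation would remove the most restless children, and that loss could itself depend on arm, with only 20 children per group.

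The cost is a few lines in the EEG script, with no change to data collection. The downsides are small: subsampling discards some surplus epochs, and debiased values are less directly comparable with published raw indices. If the indices were already to be averaged within epochs, stating so settles the point.
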